#### **15.1.7. Handling of protocol violations**

The principal investigator and the subinvestigator should be well-acquainted with the protocol and thoroughly carry out the clinical trial procedures as specified in the protocol so that any protocol violation does not occur. In order to comply with the schedules for the administration of the investigational product and tests in this clinical trial, the investigator should take appropriate measures, such as written notification or telephone monitoring related to visit time, so that the patient can attend the visit on the date. On the other hand, the inevitable protocol violation should be handled as follows:

In case of a serious violation of the clinical trial protocol, the patient should be eliminated from the analysis (excluding PPS). Refer to the items below:

- ① In case the patient has no signed consent form.
- ② In case the patient is found to have violated the inclusion/exclusion criteria
- ③ In case the patient took the prohibited concomitant medication over the duration of clinical trial
- ④ In case the primary efficacy evaluation tests at the time of the initiation-termination of this trial were missing.

When it comes to minor protocol violations, which are judged to have no effect on the interpretation of the clinical trial results, the degrees and causes of violations or delays should be exactly recorded. Whether this affected this clinical trial will be comprehensively considered through the blind meeting prior to Database Lock, and will be included in the PPS analysis.

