## **15. STATISTICAL ANALYSIS METHOD**

### **15.1. Statistical Analysis Plan**

#### **15.1.1. Definition of Analysis Set**

Analysis set is defined as follows:

- 1) Safety analysis set: the patients who have been randomized and undergone safety evaluation once or more among those who have been administered the investigational product at least once.
- 2) FAS (Full Analysis Set): the patients whose data of primary efficacy variable can be obtained among those who have been administered the investigational product at least once.
- 3) PPS (Per-Protocol Set): the patients who have completed this trial without violation of the protocol among those included in FAS group.

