#### **15.1.2. General principle of statistics**

All statistical significance tests will be conducted in the form of 2-tailed tests at the 5% significance level ( $\alpha$ ).

The major analysis of efficacy data obtained from the patients participating in this clinical trial will be carried out in the FAS in principle.

The analysis of safety data is carried out on the Safety analysis set.

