#### **15.1.6. Handling of dropouts or missing values**

If a patient who drops out of this clinical trial appears, the cause and date of dropout should be recorded in the CRF and the medical chart. If a missing value of data occurs during FAS analysis or a patient drops out of the clinical trial before its termination, the most recently

obtained data will be analyzed as if it was obtained at that relevant time (Last Observation Carried Forward Method).

However, LOCF will not be applied for PPS analysis. In case of safety evaluation items, the missing values will not be replaced.

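### Read literally, section 15.1.7 removes serious protocol violators from the main efficacy set and spares the PPS, contradicting the set definitions and the LOCF rule

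*Protocol*

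**What the plan says.** Protocol section 15.1.7 gives this rule for serious violations: "In case of a serious violation of the clinical trial protocol, the patient should be eliminated from the analysis (excluding PPS"). Four grounds follow: no signed consent, an eligibility violation, use of a prohibited medication, and, as item 4, "In case the primary efficacy evaluation tests at the time of the initiation-termination of this trial were missing". On minor violations the same section says: "Whether this affected this clinical trial will be comprehensively considered through the blind meeting prior to Database Lock, and will be included in the PPS".

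Section 15.1.1 defines the FAS as "the patients whose data of primary efficacy variable can be obtained among those who have been administered the investigational product at least once" and the PPS as "the patients who have completed this trial without violation of the protocol among those included in FAS group". Section 15.1.2 fixes the main set: "The major analysis of efficacy data obtained from the patients participating in this clinical trial will be carried out in the FAS in principle".

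Section 15.1.6 covers missing data. It begins "If a missing value of data occurs during FAS analysis or a patient drops out of the clinical trial before its termination, the most recently" and goes on to apply last observation carried forward (LOCF). It then adds that "LOCF will not be applied for PPS analysis".

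**The concern.** The parenthesis in 15.1.7 exempts the one set that is defined by the absence of violations. What remains for the elimination to act on is the FAS, and possibly the safety set, since the sentence names no set.

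Two of the four grounds arise after randomisation: prohibited medication, and a missing final SIB. Sections 7.6.2 and 14.1 tie prohibited medication to leaving the trial, so both grounds can depend on how the patient is faring. Removing such patients from the main efficacy set gives up part of the protection of randomisation and allows selection related to outcome. With about 30 patients per arm, a few removals can matter.

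**Working it through.** **1. The protocol's own figure.** Section 9.3 gives 24 evaluable patients per arm (72 in total) and 20% dropout. Inflation is n / (1 − d): 24 / 0.80 = 30 per arm and 72 / 0.80 = 90 in total. Both match the protocol, and no stated number is wrong.

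**2. The literal reading against the other sections.**
- *PPS definition.* A serious violator would leave the FAS and stay in the PPS. Section 15.1.1 draws the PPS from the FAS and admits only patients without violation. The patient therefore fails the PPS definition on both counts, and the rule cannot be carried out.
- *FAS definition.* It requires at least one dose and obtainable primary data. It has no violation criterion, so 15.1.7 would add one that 15.1.1 lacks.
- *LOCF.* The SIB is measured at Visits 2, 9 and 15 (section 12.1.1.1). Take a patient with Visits 2 and 9 but no final SIB. Under 15.1.6 the Visit 9 value is carried forward in the FAS. Under item 4 of 15.1.7 the patient is eliminated. Both instructions cannot be followed.

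**3. The alternative reading, exclusion from the PPS.** The three conflicts above disappear. Two problems remain:
- Minor violators are admitted to the PPS by 15.1.7, while 15.1.1 requires no violation at all.
- A patient without signed consent (item 1) would be dropped from the PPS only, with nothing said about the FAS or the safety set.

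**4. Size of the literal reading, item 4 alone.** Assume that every one of the planned 20% dropouts lacks a final SIB and would otherwise have had a value to carry forward.
- FAS per arm: 30 × (1 − 0.20) = 24; in total, 90 × 0.80 = 72.
- Standard error ratio: √(30/24) = 1.118, an increase of 12%.
- Detectable standardised difference, assuming 80% power with the protocol's two-sided 5% level, by normal approximation (1.960 + 0.842) × √(2/n): 0.72 at n = 30 and 0.81 at n = 24. The 80% is an assumption; section 9.3 gives no power, effect size or standard deviation.

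**5. Other serious violations.** The protocol gives no rate. If a further 5% to 20% of the remaining patients were removed, the arm would hold 24 × 0.95 = 22.8 down to 24 × 0.80 = 19.2 patients. This range is illustrative.

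**The case against.** The strongest reply is that the literal reading is not what was meant. It cannot be carried out, because the PPS lies inside the FAS. Keeping minor violators in the PPS makes sense only if serious ones are left out of it. Barring LOCF in the PPS also fits item 4 as a PPS criterion. In a translated text the parenthesis may simply mean that such patients are excluded from the PPS. This stands as the likely intention. It does not remove the defect, because no sentence states which set the elimination applies to.

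A reader might also infer several stronger points that the protocol does not support:
- *The main analysis becomes a completer analysis.* Sections 12.2.7 and 14.1 ask dropouts to have the Visit 15 tests. A dropout with a termination SIB need not fall under item 4.
- *LOCF would have no patients to act on.* Section 15.1.6 covers any missing value in the FAS, so it keeps a role for the secondary endpoints.
- *There are several competing primary populations.* Section 15.1.2 names one main set and 15.1.1 defines it. One sentence is unclear and has two readings.
- *The set could be chosen after seeing the data.* Section 15.1.7 provides a blind meeting before database lock, and section 7.5 places end-of-trial unblinding at database lock. The meeting is stated only for minor violations, so this answers the worry in part.

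Finally, 24 per arm is the protocol's own evaluable number, so the loss is relative to the FAS that LOCF could retain and is not a shortfall against plan.

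**Conclusion.** The point holds as a defect of wording in a rule that decides who enters the main efficacy analysis. Read literally, 15.1.7 is reversed. It contradicts the set definitions in 15.1.1, and item 4 collides with LOCF for a missing final SIB. Context favours exclusion from the PPS, under which the FAS is untouched by this rule.

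If the text were followed as written, item 4 could cost up to 6 of 30 patients per arm and raise the standard error by up to 12%. That bound rests on the planned 20% dropout, on no dropout having a termination SIB, and on each having an earlier value to carry forward. The real loss from item 4 should be smaller at that dropout rate. Removals for eligibility or prohibited medication would add to it, and any selection bias cannot be sized from the protocol.

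The mismatch over minor violators in the PPS holds under either reading, but it touches only a supporting set.

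**What to change.** Amend 15.1.7 to state that:
- patients with violations under items 2 to 4 are excluded from the PPS only, and every patient who meets the 15.1.1 FAS definition stays in the FAS as randomised;
- a missing final SIB is handled in the FAS by the missing-data rule of 15.1.6, while a patient with no baseline SIB, or no obtainable primary value, is governed by the FAS definition;
- item 1, missing consent, has its own rule covering the FAS, the PPS and the safety set.

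In 15.1.1, change the PPS condition to *without serious protocol violation as listed in 15.1.7*, so that minor violators may stay in the PPS.

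The cost is protocol wording only, with no added patients, visits or procedures. The change should be in place before unblinding.

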#### **15.1.8. Scheduled interim analysis and data monitoring**

The establishment of the Interim Analysis and Data Monitoring Committee was not planned in this trial. However, if a series of or a lot of unexpected serious side effects are reported, or the "unblinding" and early analysis of its results after discontinuation of this clinical trial are judged to be helpful or reduce risks for the patient, an independent data monitoring committee consisting of 3 persons or more not related to this clinical trial can be organized and operated. The establishment and organization of the committee should be implemented in accordance

with separate rules, and the committee should exclude the clinical investigator and analyze all data up to the time point of discontinuation.

## **16. SAFETY EVALUATION CRITERIA, EVALUATION METHODS AND REPORT METHODS INCLUDING ADVERSE EVENTS**

### **16.1. Definition of Adverse Events**

#### **1) Adverse Event (AE)**

AEs are defined as all harmful and unintended signs (e.g.: abnormal laboratory values), symptoms or diseases which occur in patients who are treated with the investigational product. It is not that AEs always should have causal relationship with the investigational product. AEs include but are not limited to the following items:

- Clinically significant abnormal test results
- Clinically significant symptoms or signs
- Changes in physical examination results
- Hypersensitivity
- Progress/aggravation of existing diseases.

#### **2) Adverse Drug Reaction (ADR)**

ADRs refer to all harmful and unintended reactions that are caused by a dose of the investigational product, whose causal relationship with the investigational product cannot be excluded.

#### **3) Unexpected ADR**

Unexpected ADRs mean deviation from the aspect of ADRs or the degree of their risks in view of available medication-related information such as Investigator's Brochure or Drug Labeling.

#### **4) Serious AE/ADR**

Serious AEs/ADRs refer to any of the following AEs or ADRs caused by a dose of the investigational product:

- ① In case of death or life-threatening
- ② In case the patient needs inpatient hospitalization or prolongation of existing hospitalization
- ③ In case the AEs/ADRs result in persistent or significant disability or incapacity
- ④ In case the fetus has congenital anomaly or birth defect

- ⑤ In case there are cases where other medically important situations such as drug dependence or abuse, or blood diseases, occur, in addition to the cases of ① to ④ above

In case there is a situation that is judged to have a medically significant effect on the patient's safety and health, even if it does not refer to the situations listed above, whether it is regarded as a SAE is determined under the medical judgment of the physician in charge and relevant experts, and then appropriate action should be taken accordingly.

In this clinical trial, hospitalization planned prior to participation in this clinical trial, hospitalization for beauty or convalescence purposes, hospitalization for usual treatment, etc. are not regarded as SAEs. The visit to an emergency room that lasts more than 24 hours is considered a SAE, but even if the visit to an emergency room is less 24 hours, it can be regarded as a SAE at the discretion of the investigator.

## 16.2. Collection and Recording of Adverse Events

- After randomization, AEs should be collected over the duration of this clinical trial from the time points since the administration of the investigational product to the final visit.
- AEs should be reported including the names of AEs, duration (start date and date of disappearance), severity, causal relationship with the investigational product, related measures, results, remedial treatment, and whether to have SAEs.
- When recording AEs, the investigator should record a comprehensive diagnostic name or symptom using standard medical terms rather than recording each symptom or sign.
- When it comes to AEs occurring during this clinical trial, a follow-up should be carried out until they disappear, show a stable outcome, or are lost to follow up.

## 16.3. Evaluation of Adverse Events

### 16.3.1. Severity evaluation

The severity of each AE/ADR is evaluated according to the following basis:

|                    |                                                                              |
|--------------------|------------------------------------------------------------------------------|
| Grade 1 (Mild)     | : The patient can endure it easily.                                          |
| Grade 2 (Moderate) | : Considerably hinders the patient's daily living activities                 |
| Grade 3 (Severe)   | : Impossible for the patient to engage in normal activities of daily living. |

---

The definition of activities of daily living (ADL) is as follows:

- All activities in daily life to manage one's body  
(e.g.: taking a bath, putting on and taking off clothes, eating, taking medicines, sanitation, self-help abilities)

AEs or SAEs can be all evaluated as severe according to the definition specified above, but severe adverse events do not necessarily mean serious adverse events.

#### **16.3.2. Evaluation of causal relationship**

The investigator should determine whether incidence of an AE is related with the administration of the investigational product according to the following criteria: 1) to 5) of the following criteria (Definitely related, Probably related, Possibly related, Unlikely/remote, Unassessable) are considered "related" between the administration of the investigational product and AEs; and only 6) (Definitely not related/none) is judged as "not related" between the administration of the investigational product and AEs.

##### **1) Definitely related**

- If there is evidence that the investigational product has been used
- If the time sequence between the administration of the investigational product and onset of an AE is appropriate
- If an AE is explained most plausibly by the administration of the investigational product among any other reasons
- If an AE disappears after the administration of the investigational product is discontinued
- If the outcome of rechallenge (only if possible) turns out to be positive
- If an AE shows a pattern which is consistent with the information already known about the investigational product or other medications of the same class

##### **2) Probably related**

- If there is evidence that the investigational product has been used
- If the time sequence between the administration of the investigational product and onset of an AE is appropriate
- If an AE is explained more plausibly by the administration of the investigational product than any other reason

- 
- If an AE disappears after the administration of the investigational product is discontinued

3 ) Possibly related

- If there is evidence that the investigational product has been used
- If the time sequence between the administration of the investigational product and onset of an AE is appropriate
- If it is judged that an AE is caused by the investigational product use in the same level as other potential reasons
- If an AE disappears in case the administration of the investigational product is discontinued

4 ) Unlikely/remote

- If there is evidence that the investigational product has been used
- If there is another more probable reason for an AE
- If the outcome of discontinuation of the investigational product use (if carried out) turns out to be negative or vague
- If the outcome of rechallenge (if carried out) turns out to be negative or vague

5 ) Unassessable

- If there is insufficient evidence to determine relevance
- If the quality of the evidence is low or the data is inconsistent

6 ) Definitely not related/none

- If the patient has not been treated with the investigational product
- If the time sequence between the administration of the investigational product and onset of an AE is not appropriate
- If there is another definite reason for an AE

**16.3.3. Determination of whether an AE is unexpected**

---

The investigator and GemVax & KAEL Co., Ltd. should determine whether an AE is expected or unexpected as long as it is judged as related to the investigational product.

- Expected: For the investigational product, the AEs with the nature, severity, frequency and characteristics which are consistent with them of the AEs described in the current Investigator's Brochure or the current clinical trial protocol are designated as "Expected."
  - For commercial drugs, the AEs specified in the current pharmaceutical drug's product manual or the applicable country' labeling are designated as "Expected."
- Unexpected: AEs not belonging to the scope of "Expected"

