### 13. PREDICTED ADVERSE EVENTS AND PRECAUTIONS

The safety and tolerability of the investigational product GV1001 used in this clinical trial were confirmed through previous trials. The most frequent adverse events included gastrointestinal diseases, such as nausea, vomiting, diarrhoea, abdominal pain, and fever. Serious adverse events (SAEs) reported in patients treated with GV1001 (alone or in combination with other drugs) in all GV1001 clinical trials totaled 1,418, and most SAEs (901 out of 1,418 cases) were reported in TeloVac Study.

SAEs reported most frequently in all GV1001 clinical trials are as shown in the table below:

Table 1. SAEs of GV1001 Incurred in Previous Trials

|                                                      |                             |
|------------------------------------------------------|-----------------------------|
| Gastrointestinal disorders                           | 409/1,418 cases
(28.60%) |
| Abdominal pain                                       | 80                          |
| Subileus                                             | 54                          |
| Ascites                                              | 45                          |
| Nausea                                               | 44                          |
| Constipation                                         | 27                          |
| Diarrhoea                                            | 25                          |
| Obstruction gastric                                  | 15                          |
| Vomiting                                             | 14                          |
| Duodenal obstruction                                 | 12                          |
| Etc.                                                 | 93                          |
| General disorders and administration site conditions | 280/1,418 cases
(19.58%) |

|                                       |                             |
|---------------------------------------|-----------------------------|
| Disease progression                   | 108                         |
| Pyrexia                               | 65                          |
| Device occlusion                      | 29                          |
| Pain                                  | 15                          |
| General physical health deterioration | 13                          |
| Chills                                | 8                           |

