| Fatigue                               | 8                           |
| Etc.                                  | 49                          |
| Infections and infestations           | 196/1,418 cases
(13.71%) |
| Biliary sepsis                        | 39                          |
| Sepsis                                | 22                          |
| Infection                             | 20                          |
| Lower respiratory tract infection     | 17                          |
| Pneumonia                             | 15                          |
| Cellulitis                            | 10                          |
| Urinary tract infection               | 7                           |
| Liver abscess                         | 5                           |
| Etc.                                  | 61                          |

In addition to SAEs reported frequently, erythema, soreness, pain, etc. at the injection site were reported. The injection site reactions are the side effects occurring frequently when GV1001 is administered. Generally, the reactions occur within 24 hours after the administration of GV1001 and disappear within days. Therefore, the above adverse events may occur even in this clinical trial.

If immunity-related adverse events specific to this drug appear, the administration of this drug should be discontinued, and treatments of symptoms or supportive treatments should be carried out according to the investigator's judgment while the immune response is decreasing.

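### Section 16.3.3 lets the protocol's own all-cause SAE table serve as a reference for expectedness, so a related sepsis or pneumonia could be classed as expected and miss expedited reporting

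*Protocol*

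**What the plan says.** Section 16.3.3 applies once an event has been judged related to the investigational product. It names four features to compare (nature, severity, frequency, characteristics), and events for which these are "consistent with them of the AEs described in the current Investigator's Brochure or the current clinical trial protocol are designated as 'Expected". The protocol thus stands beside the Brochure as an alternative reference. Anything outside that scope is unexpected.

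Section 16.1(3) defines an unexpected ADR as one that departs in aspect or degree of risk "in view of available medication-related information such as Investigator's Brochure or Drug Labeling". It does not name the protocol.

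Section 13, on predicted adverse events, introduces Table 1 with "SAEs reported most frequently in all GV1001 clinical trials are as shown in the table below". The 1,418 SAEs come from patients given GV1001 alone or in combination, and no causality filter is stated. After Table 1 the section turns to injection-site reactions and then concludes: "Therefore, the above adverse events may occur even in this clinical trial".

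Two provisions depend on the word unexpected. Section 16.4 sets regulatory deadlines of 7 days (fatal or life-threatening) and 15 days (other) for serious unexpected ADRs. Section 15.1.8 plans no data monitoring committee but allows one "if a series of or a lot of unexpected serious side effects are reported", or if unblinding and early analysis after discontinuation is judged helpful or risk-reducing.

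**The concern.** A reference for expectedness should describe reactions attributed to the product. Table 1 instead counts serious events of any cause. Disease progression and device occlusion are plainly not described there as reactions to GV1001, and nothing in the protocol says that the sepsis or pneumonia cases were. Section 5.1.2 names anticancer indications for the earlier trials, whereas this trial enrols patients with Alzheimer's disease.

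If such a table may be used under 16.3.3, a serious infection judged related to GV1001 in this trial can be called expected because its term appears in section 13. It would then fall outside the expedited route to the regulator and would not count towards the 15.1.8 trigger. Expectedness carries much of the weight here because 16.3.2 counts even unlikely and unassessable events as related. The causality step therefore removes few events, and expectedness is the main filter between an SAE and a SUSAR.

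**Working it through.** The question is mainly textual. Arithmetic serves only to show what Table 1 covers.

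**1. Can Table 1 be a reference?** Section 16.3.3 admits AEs described in the current protocol. Section 13 of that protocol describes SAEs under a title about predicted events. Nothing in section 13 or 16.3.3 says that Table 1 is background only. So the wording allows it.

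**2. Is Table 1 a list of reactions?** No causality filter is stated, and combination treatment is included. Section 5.1.2 also says that serious side effects have not been reported in GV1001 trials. On the protocol's own account, then, Table 1 cannot be a list of known serious reactions.

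**3. Can the four-part test be applied from Table 1?** Section 16.3.3 requires consistency on all four elements.

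| Element required | What Table 1 offers |
|---|---|
| Nature | Event term and organ class |
| Severity | No grade or outcome |
| Frequency | Case counts and shares of SAEs, with no number of patients treated |
| Characteristics | Nothing beyond the term |

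A count out of 1,418 SAEs is not a rate per patient treated, so no observed frequency in this trial can be compared with it. Table 1 supports a term match and nothing more.

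**4. How much does Table 1 cover?**

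- Gastrointestinal: 9 named terms, 80+54+45+44+27+25+15+14+12 = 316; plus 93 unnamed = 409 (printed 409).
- General disorders: 7 named terms, 108+65+29+15+13+8+8 = 246; plus 49 unnamed = 295 (printed 280).
- Infections: 8 named terms, 39+22+20+17+15+10+7+5 = 135; plus 61 unnamed = 196 (printed 196).
- Named terms: 9+7+8 = 24, holding 316+246+135 = 697 cases; 697/1,418 = 49.2%.
- Printed class totals: 409+280+196 = 885; 885/1,418 = 62.4%. The other 1,418−885 = 533 fall in no listed class.
- Sepsis 22/1,418 = 1.6%; pneumonia 15/1,418 = 1.1%.
- One earlier study supplied 901/1,418 = 63.5% of the SAEs. The protocol does not state its population.

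**5. The printed percentages.** On the stated denominator: 409/1,418 = 28.84% (printed 28.60%), 280/1,418 = 19.75% (printed 19.58%), 196/1,418 = 13.82% (printed 13.71%). All three printed values are reproduced with 1,430: 409/1,430 = 28.60%, 280/1,430 = 19.58%, 196/1,430 = 13.71%. These errors, and the 295 against 280, are clerical. The argument in steps 1 to 3 does not depend on them.

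**6. Are 16.1(3) and 16.3.3 in conflict?** One gives the Brochure and labelling as examples; the other adds the protocol. The examples in 16.1(3) are introduced as open-ended, so the two can be read together. They can also be read apart: an assessor who works from the Brochure alone and one who also accepts Table 1 may class the same event differently. This is an ambiguity, not a flat contradiction.

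**The case against.** The strongest reply is that 16.3.3 already protects against misuse. A mention in the protocol is not enough: nature, severity, frequency and characteristics must all be consistent. If Table 1 cannot show that match, the event falls outside the expected class and is unexpected by default, so it would be reported. Read strictly, this is correct. It rules out the stronger inferences that every event in Table 1 is expected, or that a related sepsis or pneumonia would certainly not be a SUSAR. It does not remove the defect. The rule names a reference on which its own test cannot be carried out, and leaves assessors to settle for a term match or to guess.

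Other replies also stand in part:

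- A reader might take Table 1 to list all earlier serious events. It does not; it gives the most frequent ones. The 93+49+61 = 203 unnamed cases are not described and cannot make anything expected.
- Safeguards remain that do not depend on expectedness. Under 16.4 all SAEs go to the sponsor within 24 hours whether related or not, and to the IRB under institutional rules; investigators must report serious ADRs immediately. Section 15.1.8 has a second, judgement-based route to a committee. These soften the consequence but do not replace the regulatory deadlines.
- The closing sentence of section 13 directly follows the injection-site text, so it may refer to those reactions only. The point does not need it, because 16.3.3 refers to AEs described in the protocol, whether or not they are forecast.
- The Brochure is not shown. It may list some of the same terms, in which case they could be expected regardless.

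**Conclusion.** The point holds in a limited form. Section 16.3.3 admits the protocol as a reference for expectedness, and the protocol's only serious-event listing is unfiltered for cause and cannot support the severity and frequency comparison that 16.3.3 requires. A serious event judged related, such as sepsis or pneumonia, could be classed as expected on its term alone. It could then miss the 7- or 15-day report and the event-count trigger in 15.1.8.

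The exposure is up to 24 named terms. How many events in this trial would be affected cannot be estimated from the document. The conclusion assumes that an assessor may use Table 1, which the text permits, and that the Brochure does not already list the event as a known reaction, which cannot be checked here. That the earlier trials were largely anticancer trials is a fair inference from section 5.1.2, but the conclusion does not rest on it.

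**What to change.** - Sections 16.1(3) and 16.3.3: state one and the same reference for expectedness, and remove the current protocol from 16.3.3. The Brochure is the natural candidate, since both sections already name it. The sponsor should confirm that it identifies reactions considered related to GV1001; if it only repeats all-cause SAEs, the wording change will not be enough.
- Section 13: state that Table 1 is all-cause background from earlier trials and is not a basis for judging expectedness.
- Separately, and minor: correct Table 1. Reconcile the general disorders rows (295) with the printed 280, and the percentages with the stated denominator of 1,418.

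The cost is a change of protocol wording and possibly a few more expedited reports. Sample size, schedule and analysis are untouched.
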